## Abstract

**Background:**

Hemodialysis (HD) is a common renal replacement therapy for patients with renal failure. Cardiovascular and cerebrovascular diseases are known to shorten survival periods and worsen the quality of life of HD patients. Atherosclerosis is a major cause of vascular diseases, and various factors such as abnormality of lipid metabolism and increased macrophage activity, oxidative stress, and endothelial dysfunction are associated with its pathogenesis and progression. Further, endothelial stem cells (ESCs) have been reported to play important roles in endothelial functions. Royal jelly (RJ) affects atherosclerosis- and endothelial function-related factors. The main aim of this trial is to investigate whether oral intake of RJ can maintain endothelial function in HD patients. In addition, the effects of RJ intake on atherosclerosis, ESC count, inflammation, and oxidative stress will be analyzed.

**Methods:**

This will be a multicenter, prospective, double-blind, randomized controlled trial. We will enroll 270 participants at Nagasaki Jin Hospital, Shinzato Clinic Urakami, and Maeda Clinic, Japan. The participants will be randomized into RJ and placebo groups. The trial will be conducted according to the principles of the Declaration of Helsinki, and all participants will be required to provide written informed consent. The RJ group will be treated with 3600 mg/day of RJ for 24 months, and the placebo group will be treated with starch for 24 months. The primary endpoint will be the change in flow-mediated dilation (FMD), a parameter of endothelium function, from the time before treatment initiation to 24 months after treatment initiation. The secondary and other endpoints will be changes in FMD; ESC count; serum levels of vascular endothelial cell growth factor, macrophage colony-stimulating factor, 8-hydroxydeoxyguanosine, and malondialdehyde; the incidence of cardiovascular diseases, cerebrovascular diseases, and stenosis of blood access; and safety.

**Discussion:**

This trial will clarify whether oral intake of RJ can maintain endothelial function and suppress the progression of atherosclerosis in HD patients. In addition, it will clarify the effects of RJ on ESCs, oxidative stress, and angiogenic activity in blood samples.

**Trial registration:**

The Japan Registry of Clinical Trials jRCTs071200031.  Registered on 7 December 2020.

## Background

Hemodialysis (HD) is used as renal replacement therapy for the control of uremic syndrome in patients with renal failure. With the development of dialysis medicine, including devices, dialysates, and drugs, the survival period and quality of life (QoL) of HD patients have improved. However, various HD-related complications, especially cardiovascular and cerebrovascular diseases, shorten the survival periods and worsen the QoL in HD patients [1, 2]. Many factors, such as hypertension, hyperlipidemia, and uremia, are associated with the pathogenesis of vascular damage by complex mechanisms [3]. Furthermore, there is general agreement that atherosclerosis plays a crucial role in the development of vascular diseases and results in increased mortality among HD patients [4, 5]. Thus, an understanding of the detailed pathological mechanism of atherosclerosis and the development of therapeutic approaches for such pathological conditions are essential for improving the survival and QoL of these patients.

The pathophysiological mechanism of atherosclerosis has been well-studied worldwide, and many investigators suggest that the following four factors are strong determinants of the occurrence and development of atherosclerosis: (1) abnormal lipid metabolism, including oxidation of low-density lipoprotein (LDL) cholesterol, is an important step in the occurrence of atherosclerosis [6]; (2) differentiation and activation of macrophages play crucial roles in lipid homeostasis in atherosclerotic lesions [7]; (3) dysfunction of endothelial cells and injury to the arterial intima lead to cholesterol accumulation and formation of foam cells from infiltrated macrophages [7, 8]; and (4) inflammation and oxidative stress strongly regulate such pathological processes by a coordinated system [8, 9]. In addition to these representative atherosclerosis-related factors, several other factors are associated with the pathogenesis and development of atherosclerosis. For example, endothelial stem cells (ESCs) play an important role in vascular repair, especially when endothelial damage is severe [10]. Moreover, macrophage colony-stimulating factor (MCSF), which is a strong stimulator of macrophage differentiation and activity, is associated with atherosclerosis under various pathological conditions, including HD [11, 12]. Interestingly, MCSF has been reported to be associated with the differentiation, migration, and secretory capacity of ESCs [13–15]. Oxidative stress is also induced by the differentiation, survival, and activity of ESCs [16, 17]. However, the detailed clinical role of ESCs in the repair of vascular function in HD patients has not been studied.

Royal jelly (RJ) is a natural bee product that is widely used as a health food and supplement worldwide because of its anti-inflammatory, antioxidative, antibacterial, and anticancer effects [18, 19]. In addition, RJ has been reported to be associated with vasorelaxation and anti-hypertensive effects via vascular endothelial cell activity, angiogenesis, and nitric oxide production at the molecular level [20–23]. Moreover, several in vitro studies have shown that RJ affects the secretion of inflammation-related cytokines from activated macrophages [24, 25]. Unfortunately, little information is available on the association between RJ administration and inflammation-related cytokines in humans. However, oral intake of RJ can suppress anticancer agent-induced adverse events by regulating inflammation-related cytokines [26].

Therefore, in addition to its use in traditional medicine, RJ is administered as a modern therapeutic agent for various diseases, such as hypertension, hypercholesterolemia, and malignancies [19, 27]. However, a direct correlation between RJ and MCSF in humans has not been established. Interestingly, we found that the serum levels of MCSF changed after the oral intake of RJ in renal cell carcinoma patients treated with tyrosine kinase inhibitors (unpublished data). Based on these facts, RJ was speculated to affect various atherosclerosis-related factors, including inflammation, oxidative stress, endothelial function, and ESC activity. Therefore, this trial will be conducted to verify our hypothesis that oral intake of RJ is effective in improving vascular endothelial function, and consequently, suppressing the risk of cardiovascular and cerebrovascular diseases via regulation of inflammation, oxidative stress, and the activities of macrophages and ESCs in chronic HD patients.

## Methods

### Study design

This clinical trial will be conducted in a multicenter, randomized, double-blind, placebo-controlled setting. The study is planned to investigate the superiority of RJ compared to placebo. Three institutions in Japan (Shinzato Clinic Urakami, Maeda Clinic, and Nagasaki Jin Hospital) will participate in this trial. Our RJ is the same as the commercial supplement manufactured in Yamada Bee Farm, and the recommended dosage of this supplement is 3600 mg/day. Therefore, in this trial, HD patients will be divided into two groups: the RJ group, which will be treated with 3600 mg/day of RJ for 24 months, and the placebo group, which will be treated with starch for 24 months. Both RJ and placebo were provided by the Institute for Bee Products and Health Science (Okayama, Japan). The flow chart and timeline of this study are shown in Figs. 1 and 2. The trial has been approved by the certified institutional review board of Nagasaki University Hospital (no. CRB7180001), and the protocol has been registered in the University Hospital Medical Information Network (UMIN000020152) and The Japan Registry of Clinical Trials (jRCTs071200031). In case of protocol modification, the contents of the change will be shown to relevant parties after approval by our IRB. There was no additional collection and use of participant data and biological specimens in ancillary studies. There will be no post-trial care. The individual data will not be disclosed to sponsor, participants, healthcare professionals, the public, and other relevant groups. On the other hand, analyzed data of all participants will be disclosed to all of these groups via publication and public-relation magazine. The full protocol, participant-level dataset, and statistical code will not be disclosed.

**Fig. 1 Fig1:**
[figure not shown]
Flow chart of our study

**Fig. 2 Fig2:**
[figure not shown]
Timeline for all study patients

Consent about the planned storage of the biological samples will be obtained by the same consent form in this trial. However, we stated in the form that additional consent or opt-out would be necessary for the biological samples to be used for further analyses.

### Randomization

Randomization will be performed by an independent employee of Nagasaki University Hospital using the envelope method, and medical investigators at each institute will be responsible for allocating patients. In short, eligible patients will be randomly assigned in a 1:1 ratio using a computerized random number generator, and the allocation information will be placed in sealed envelopes. Each patient will be assigned a unique number to protect their personal information. The randomized list will be managed by only an independent data manager and will be concealed from all investigators and patients. All information regarding patient selection will remain confidential and unknown to all investigators, including outcome assessors and statisticians, until the completion of the trial. Emergent unblinding will not be possible in this trial.

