### Follow-up

The patients will visit the hospital 3–4 times per week for maintenance HD. The frequency of HD in a week will be determined by medical judgment based on laboratory data, clinical practice, and patient wishes. Similarly, decisions about the contents of HD will be made according to each institution’s policy independent of this trial. There are no relevant concomitant care and interventions that are permitted or prohibited during the trial.

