### Statistical analyses

The results of all examinations will be expressed as mean ± SD. To clarify the primary endpoint, the changes in the rates of FMD after treatment for 24 months (FMD for 24 months/baseline) will be compared between the RJ and placebo groups using the Student’s *t* test. Non-adherence and missing data will not be used in this analysis. A similar analysis will be performed to compare the changes in FMD at 6, 12, and 18 months between the two groups. For this analysis, missing data will be used according to the period of RJ administration. Other variables and data will be analyzed similarly at 6, 12, 18, and 24 months. There is no plan for any additional analyses. Permitted investigators (KO, YM, TM, KM) will have access to these interim results.

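### Dialysis care is set by institution, yet the fixed primary t test takes no account of institution: a small, cheaply avoided loss of precision, not a bias

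*Protocol article*

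**What the plan says.** Study design: "Three institutions in Japan (Shinzato Clinic Urakami, Maeda Clinic, and Nagasaki Jin Hospital) will participate in this trial". Enrolment per institution is not given.

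Follow-up: "decisions about the contents of HD will be made according to each institution’s policy independent of this trial". The same section adds: "There are no relevant concomitant care and interventions that are permitted or prohibited during the trial".

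Randomization: "eligible patients will be randomly assigned in a 1:1 ratio using a computerized random number generator", using sealed envelopes, and "medical investigators at each institute will be responsible for allocating patients". The section presents this as a summary. It mentions neither stratification nor blocking, and it does not say whether each institution has its own set of envelopes.

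Statistical analyses: the 24-month/baseline FMD ratio "will be compared between the RJ and placebo groups using the Student’s" t test. Other variables are to be handled in the same way, and "There is no plan for any additional analyses".

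The section on cardiovascular diseases, cerebrovascular diseases and stenosis of blood access counts arrhythmia only if it needed medical treatment, and access stenosis only if it needed a balloon procedure or surgery. Both depend partly on local decisions to treat.

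**The concern.** Institution is the one source of differing background care that the article itself identifies. It acts throughout treatment and could affect both the change in FMD and the threshold at which an event is treated and so counted. The stated analysis neither uses institution nor leaves room for doing so later. If outcomes differ between institutions, that variation widens the confidence interval for the treatment difference. An uneven mix of institutions between arms would also go uncorrected. The sample size section concedes that little is known about the effect of royal jelly on FMD, so precision that can be had almost free is worth having.

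**Working it through.** **Inputs from the article.** Alpha 0.05, power 0.8, 112 per group, about 20% incomplete data and 135 per group (Sample size); three institutions (Study design); unadjusted t test (Statistical analyses).

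**Assumptions.** Two-sided test; the share r of outcome variance explained by institution; the number of patients per institution. The article gives none of these.

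**Step 1: the plan's own figure.** The 112 cannot be rebuilt, because no effect size or SD is printed. Solving backwards, it implies a standardised effect of d = (1.960 + 0.842) × √(2/112) = 0.374. The 135 matches 112 × 1.2 = 134.4. The point does not depend on either figure; d serves only as a reference for power.

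**Step 2: power gained by adjusting.** With institution in the model, the residual SD falls by a factor √(1 − r), so power = Φ(2.802/√(1 − r) − 1.960) at 112 per group.

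| r (assumed) | 2.802/√(1 − r) | Power |
|---|---|---|
| 0 | 2.802 | 80% |
| 0.02 | 2.830 | 81% |
| 0.05 | 2.874 | 82% |
| 0.10 | 2.953 | 84% |
| 0.15 | 3.039 | 86% |

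A simulation of simple randomisation (224 analysed, assumed split 124/62/38, 10,000 runs per setting) gave adjusted against unadjusted power of 81.1% against 79.2% at r = 0.05, and 83.6% against 79.8% at r = 0.10. At r = 0 the two were 79.1% and 79.4%, so the cost of an unneeded term is negligible.

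**Step 3: type I error of the planned test.**
- Simple randomisation: simulated error of the unadjusted t test was 4.9% to 5.2% for r from 0 to 0.20. The test is valid.
- Randomisation stratified by institution: the true variance of the treatment difference falls by the factor (1 − r), but the t test still uses the full variance. The error is then about 2 × [1 − Φ(1.960/√(1 − r))], which is 4.4%, 3.9% and 2.8% at r = 0.05, 0.10 and 0.20 (simulated 4.2%, 3.9% and 2.9%). The test is conservative.

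**Step 4: chance imbalance in institution mix.** Take three institutions of 90 (assumed) and the planned 135 per group. The number on royal jelly at one institution then has SD √(135 × 1/3 × 2/3 × 135/269) = 3.88 and a 95% range of 37 to 53. A between-arm difference of 18 or more at an institution means 36 or fewer, or 54 or more, on royal jelly. By simulation, at least one of the three institutions reaches this in about 7% of trials.

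**The case against.** Three stronger readings are tempting, and the article supports none of them.

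- **That patients are randomised from a plain, unstratified list.** This would be inferred from silence. The method is given in summary, a condensed article may leave stratification to the full protocol, and allocation at each institute is compatible with institution-specific envelopes. The sentence on the 1:1 draw contains no error.
- **That institution-specific care biases the comparison.** Both arms within an institution receive the same policy under double blinding. A chance shift in institution mix is already covered by the standard error, as Step 3 shows. The same holds for local treatment thresholds in the event definitions: they add noise, not bias.
- **That serious imbalance is likely.** Independent coin tosses at three institutions of 90 would give a difference of 18 or more somewhere in about 20% of trials. That lets the arm totals drift, whereas the plan has 135 in each group; with those totals the figure is about 7%.

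It is also fair to say that all FMD measurements are made by one blinded investigator, and that each patient's result is taken relative to baseline. Both shrink any institution effect on the primary endpoint. Neither removes an effect of institution on change over 24 months, and neither helps with the events.

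What remains of the other side is that an unadjusted t test is a valid choice and that the article offers no evidence that institution matters. That limits the point to efficiency. It does not dispose of it, because the analysis without institution is stated outright and further analyses are ruled out.

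**Conclusion.** The point stands as a minor one, and it rests on the stated analysis, not on the randomisation sentence. Institution should be in the primary comparison whichever way the list was made: under simple randomisation it recovers precision, and under stratified randomisation it makes the analysis match the design and restores the nominal error rate. The gain is about 1 to 6 points of power if institution explains 2% to 15% of the outcome variance, and nothing if it explains none. Those shares, the two-sided test and the institution sizes are assumptions. Nothing here suggests that the planned result would be biased.

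**What to change.** Before unblinding:

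1. Replace the primary t test with a linear model for the same FMD outcome, containing treatment and institution.
2. Stratify or adjust the event comparisons by institution.
3. State whether randomisation is stratified by institution. If it is not, draw separate permuted-block lists per institution for any patients still to be randomised, with block sizes known only to the independent data manager. The article expected recruitment to end on 7 December 2022, so this part may no longer apply; the first two parts do not depend on it.

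The analysis change costs two degrees of freedom (three institutions) and needs no extra patients or visits. New lists, if still relevant, would cost one further preparation of envelopes by the independent employee. If only the randomisation were stratified and the t test kept, the test would be conservative, so stratified lists should not be adopted without the model change.

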### Exclusion criteria

The exclusion criteria are as follows.
Patients who already consume RJ or original bee food products.Patients who plan to consume RJ during the trial period.Patients with severe vascular diseases that need treatment.Patients allergic to RJ or original bee food products.Patients with a history of asthma or atopic dermatitis.Pregnant or lactating patients.Patients who are judged as unsuitable for inclusion in the trial by the principal investigator or co-investigators.

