### Sample size

Unfortunately, there are no reports on changes in FMD due to oral intake of RJ in HD patients. In addition, temporal changes in FMD during HD sessions are unclear. There is general agreement that RJ is a safe food, and our study design poses an extremely low risk to patients as the only other invasive intervention will be the collection of a blood sample (20 ml) every 3 months. Considering these aspects, the proposed sample size was calculated according to the expected agreement rates (60%) of patients, which is the object of this trial. Finally, 135 patients will be enrolled in each of the two groups. For recruitment, the posters that showed purpose, method, risk, and cost are displayed. All authors will obtain written informed consent from potential trial participants or authorized surrogates after oral explanation and providing the explanatory documents. The consent form is original, and it has been approved by our IRB.

We also calculated the proposed sample size according to a previous paper on FMD in HD patients and a meta-analysis of changes in FMD associated with the oral intake of another supplement (magnesium) [30, 31]. In short, 112 patients will be enrolled in each group (a total of 224 patients) with an alpha error rate of 0.05 and a power of 0.8. This is because incomplete data may be available for some patients (approximately 20% of the patients), and patient dropouts may occur before the completion of the trial. Finally, we plan to enroll 135 patients in each group. Regarding such processes, we have had repeated discussions with several biostatisticians. In addition, our decision on sample size was reviewed twice by IRB members, including other biostatisticians. Finally, this policy was approved by IRB because of limited information about the influence of RJ on FMD and the high safety of RJ.

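### The Randomization section rules out emergency unblinding absolutely, so a physician treating a suspected severe reaction cannot learn what the participant took until the trial is over

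*Protocol article*

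**What the plan says.** All references are to the protocol article.

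- **Randomization.** Allocation is 1:1 by computer-generated numbers, with sealed envelopes. On custody: "The randomized list will be managed by only an independent data manager and will be concealed from all investigators and patients". Investigators, outcome assessors and statisticians stay blinded until the trial is complete. The section closes with: "Emergent unblinding will not be possible in this trial".
- **Exclusion criteria.** Two entries concern allergy or atopy: "Patients allergic to RJ or original bee food products" and "Patients with a history of asthma or atopic dermatitis".
- **Study design.** On the product: "Our RJ is the same as the commercial supplement".
- **Safety management.** A serious adverse event (SAE) suspected of being due to RJ leads to the product being stopped. If a causal relation to RJ exists, the study ends. Site investigators judge relatedness and report to the ethics committee within 24 h. A further sentence, read literally, obliges the principal investigator to end the trial when a single investigator proposes this on account of SAEs. That sentence does not mention relatedness to RJ.

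**The concern.** A double-blind trial of a product with a foreseen allergic risk normally keeps a route by which one participant's allocation can be released when care depends on it. Here the article closes that route in so many words. It is therefore a stated rule, and not a detail that a condensed article has left out: a code-break procedure in the full protocol would contradict the sentence.

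What is at stake is the care of an individual participant. Stopping the product ends exposure, but it leaves two questions open: must this patient avoid RJ from now on, and should some other cause of the reaction be looked for? If the participant was on RJ, the first question becomes pressing. If on starch, RJ is ruled out as the cause and the second does.

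**Working it through.** The plan gives no figure on this point, so the check is a reading of the sections side by side, followed by what little can be sized.

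**1. Is unblinding impossible in practice or only forbidden?** The Randomization section places the list with an independent data manager. Someone outside the investigator team can look up any participant's arm, so the barrier is the rule.

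**2. Does the protocol foresee an event for which allocation matters?** Yes. It excludes people with known allergy to RJ or bee products and people with asthma or atopic dermatitis. These exclusions lower the risk but do not remove it, since a first reaction can occur in someone with no known history.

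**3. What does the physician have after such an event?** Safety management provides for stopping the product and reporting. It does not provide the allocation, and Randomization forbids obtaining it urgently.

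**4. How long could the question stay open?** Inputs from Trial status: recruitment started in December 2020 and was expected to end on 7 December 2022; final follow-up was expected to end on 31 December 2024. I assume that trial completion means the end of final follow-up.

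- Reaction soon after entry, earliest participants: December 2020 to 31 December 2024, about 48 months.
- Reaction soon after entry, last participants: 7 December 2022 to 31 December 2024, just under 25 months.
- Reaction at the end of 24 months of treatment, earliest participants: 48 − 24 = about 24 months.
- Reaction at the end of treatment, last participants: close to zero.

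**5. How uncertain is the physician?** The Randomization section says "eligible patients will be randomly assigned in a 1:1 ratio" and the Sample size section says "135 patients will be enrolled in each of the two groups". Before any clinical evidence, the chance that a participant is on starch is 135/270 = 0.50. Going further needs an assumption. If blinded judgements of an RJ-related SAE arise R times as often on RJ as on starch, with equal follow-up, the share falling on starch participants is 135/(135 + 135R) = 1/(1 + R):

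| Assumed R | Share on starch |
|---|---|
| 1 | 50% |
| 2 | 33% |
| 4 | 20% |
| 9 | 10% |

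R is not in the documents. The table shows only that a blinded attribution can leave real doubt. It is neither the frequency of such events nor the chance that the trial is stopped.

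**6. Is the primary comparison affected?** The FMD measurement section has a single investigator, blinded to clinical details, make all measurements. Neither the present rule nor a controlled code-break to the treating physician need reach that person.

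**The case against.** **The case for leaving the rule alone.** Stopping the product is often adequate acute care, and the physician can advise avoiding RJ as a precaution without knowing the arm. The Sample size section describes RJ as a safe food, and the review board approved the trial with that in mind. The exclusions make allergic reactions less likely, and the harm is delay, since concealment lasts only until completion. All of this is fair and limits the expected frequency. It does not justify forbidding a safeguard that would then seldom be used, and precautionary avoidance does not tell the physician whether to seek another cause.

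**Stronger readings that the documents do not support.**

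- *A reader might infer that the Randomization and Safety management sections contradict each other.* They do not. Blinded judgement of causality is routine, the stopping rule can be carried out, and nothing bars the data manager from informing the ethics committee.
- *A reader might infer that no one would check the arm before ending the trial.* The article states no such check, but this is partly operational detail that the full protocol may hold. It supports a secondary safeguard, not the main finding.
- *A reader might take the following as barring patients from ever learning their own allocation:* "The individual data will not be disclosed to sponsor, participants, healthcare professionals, the public, and other relevant groups". In context it reads as a data-sharing statement: it is followed by the disclosure of analysed data and the non-disclosure of the dataset and code. The point does not rest on it.
- *A reader might infer that the trial is likely to be stopped by an event in a starch participant.* No rate of SAEs or of attribution is given, so no such probability can be stated. How low to set the stopping threshold is a choice for the sponsor and the review board.

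**Conclusion.** The point holds in a limited form. The absolute exclusion of emergency unblinding is a stated defect in patient safety and should be corrected. Until trial completion it denies the treating physician information that the data manager already holds and that bears on future avoidance and on the search for another cause.

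Its size can be given only as a possible delay, from near zero to about four years on the planned dates, assuming that completion means the end of final follow-up. The frequency cannot be derived from the documents. The FMD comparison is not biased, and the conclusion does not depend on any assumed SAE rate or on R.

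**What to change.** Replace the last sentence of the Randomization section with:

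> When a participant's safety requires it, the independent data manager will disclose that participant's allocation to the treating physician; outcome assessors, statisticians and other investigators remain blinded, and each disclosure is recorded.

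As a secondary safeguard, add to Safety management:

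> Before any termination of the trial because of a serious adverse event, including one proposed by a single investigator, the data manager reports the affected participant's allocation to the ethics committee.

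The second sentence must cover every SAE-driven termination. A check limited to events judged RJ-related would miss the single-investigator trigger. The stopping criteria themselves stay with the sponsor and the review board.

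The cost is a short amendment through the review-board route that the Study design section already describes, using the existing list holder and the existing 24 h report. A few participants may be individually unblinded, and the data manager must be reachable when needed.
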